### Process evaluation

An extensive process evaluation will be conducted based on two complementary pillars: 1) Stecklar and Linnan’s framework [81] and its adaptations by Murta, Sanderson and Oldenburg [82], and 2) a selection of Randall, Nielsen and Tvedt’s Intervention Process Measure (IPM) [83]. The first pillar helps to answer instrumental questions concerning the intervention process (how does the intervention work?). The second pillar helps to identify participants’ appraisals of the intervention process (why does the intervention work?). A combined approach seems necessary to answer both the “how” and “why” question, since some studies have shown that an equal amount of ‘dose received’ can yield a range of heterogeneous individual appraisals of the intervention [84]. And the appraisal of intervention processes may in turn influence intervention outcomes [85].

Stecklar and Linnan [81] propose seven components to determine how the intervention was implemented (Table 1): (i) recruitment (what procedures were used to interest workers and what are reasons for not participating?), (ii) reach (attendance of workers in each phase of the participatory approach and its consequent tailored measures), (iii) dose delivered (how many steps of the participatory approach were actually delivered by the facilitator?), (iv) dose received (how many steps of the participatory approach were actually followed by the worker?), (v) fidelity (was the participatory approach delivered according to protocol?), (vi) satisfaction (how satisfied are participants with the participatory approach?); and (vii) context (what organizational and environmental characteristics affect the intervention?).

**Table 1 T1:** Process evaluation components and (examples of) questions

**Ref.**	**Components**	**Questions**	**Logs researcher**	**Logs facilitator**	**Interviews**	**T1**	**Group interviews**	**T2**
[81,82]	*Recruitment*	what procedures were used to interest workers and what are reasons for not participating?	X					
[81,82]	*Reach*	attendance of workers in each phase of the participatory approach and its consequent tailored measures			X	X	X	X
[81,82]	*Dose delivered*	how many steps of the participatory approach were actually delivered by the facilitator?	X		X			
[81,82]	*Dose received*	how many steps of the participatory approach were actually followed by the worker?		X		X		
[81,82]	*Fidelity*	was the participatory approach delivered according to protocol?	X		X	X	X	X
[86]	*Satisfaction*	how satisfied are participants with the participatory approach?			X	X	X	X
[84,86]	*Context*	what organizational and environmental characteristics affect the intervention?	X		X		X	
[84]	*Line manager attitudes and actions*	e.g. “My immediate manager has done a lot to involve employees throughout the process”				X		X
[84]	*Exposure to components of the intended intervention*	e.g. “The project has made it easier to tackle the changes in the organization”				X		X
[84]	*Employee involvement*	e.g. “I had the opportunity to give my views about the change before it was implemented”				X		X
[84]	*Employee readiness for change*	e.g. “I looked forward to the changes brought about by the project”				X		X

Randall and colleagues [83] have shown that participants’ appraisals of an intervention and its implementation can be measured quantitatively by the five scales of the Intervention Process Measure, of which four are used and adjusted to fit this study (Table 1): (a) line manager attitudes and actions, (b) exposure to components of the intended intervention, (c) employee involvement, and (d) employee readiness for change. Scores on these scales will be related to intervention outcomes (e.g. job satisfaction, well-being, and self-efficacy).

Six sources of data are used to assess the proposed process aspects (Table 1): (1) data logs by the researchers (recruitment, dose delivered, fidelity, context); (2) logs by the facilitator (dose received); (3) interviews at T1 with employees, management, participatory group and facilitator (reach, dose delivered, fidelity, satisfaction, context); (4) questionnaire at T1 (reach, dose received, fidelity, satisfaction, line manager attitudes and actions, exposure to components of the intended intervention, employee involvement and employee readiness for change; (5) separate group interviews with employees and management at T2 (reach, fidelity, satisfaction, context); (6) questionnaire at T2 (reach, fidelity, satisfaction, line manager attitudes and actions, exposure to components of the intended intervention, employee involvement and employee readiness for change). Data will be analyzed by either qualitative data software (e.g. Kwalitan) or by using a qualitative rating procedure.

### Ethical considerations

The study protocol and materials are approved by TNO’s Review Committee Participants in Experiments (RCPE), an internal ethics committee that assesses ethical aspects of working with participants in experiments. After review, the committee stated that in this study “the information is complete, participants can join voluntarily and an informed consent is provided”. The RCPE has thus given a positive advice to the study’s responsible manager, who decided to follow the positive approval by giving permission for performing the study. Hereafter we will elaborate on the information provision prior to and during the study.

#### Information provision prior to the study

Prior to the study, higher management of both schools signed a letter of intent to participate, cooperate and invest in kind. At the start of the project, a more detailed project plan will be presented to higher management in both schools where after working arrangements are made.

#### Information provision on measurement

Prior to baseline measurement employees in the intervention and control group will receive verbal and written information on the baseline measurement. Employees in the intervention group will be informed verbally by the participatory group (Engine of Development) by presentations at team meetings. Employees in the control group will be informed by their immediate supervisors during team meetings. Management in both the inter2vention and control group will be informed by the facilitator during a management meeting. All groups will receive a digital letter with information about the baseline measurement.

Furthermore, the agenda of a team meeting will be cleared, to enable employees to fill out the questionnaire(s) during this time frame.

All employees and managers participating in the baseline measurement are requested to sign an informed consent at the start of the questionnaire. By signing the informed consent participants declare amongst other things: 1) to have received information on the baseline measurement and the study, 2) to understand they can withdraw at any time from the study without reason. A similar procedure will be applied for the first follow-up (T1, 6 months) and second follow-up (T2, 18 months).

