#### Phase 1: Needs assessment

The needs assessment is conducted in the tradition of participatory action research (PAR) [39]. Therefore, a participatory group of employees is constituted, comprising employees, a representative from the Workers Council, a staff member, a management member, the HM-facilitator and the researcher (six to eleven members in total). Its members are selected by the management team (with the exception of the facilitator and the researcher), based on their perception of the member’s capacity for ‘pioneering’ in organizational change processes. The HM-facilitator is an expert in organizational change processes. If the intervention group is scattered among several school locations, this will be taken into account when composing the group. The participatory group is named ‘Engine of Development’ and becomes the project’s ambassador throughout the needs assessment. The Engine of Development decides in collaboration how often they meet, but at least six times – before, during and after the three needs assessment steps.

The intervention kicks off with an information session, held after baseline measurement, led by the HM-facilitator and facilitated by the management. In the information session the HM-facilitator outlines the steps of the upcoming intervention and the researcher presents several outcomes of the baseline measurement.

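### Before T0, intervention staff are briefed by the Engine of Development and control staff by their supervisors, so the messenger differs by arm before the baseline is measured

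*Protocol article*

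**What the plan says.** Three parts of the Protocol article bear on this point.

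- **Information provision on measurement** (under Ethical considerations) sets the timing and subject: "Prior to baseline measurement employees in the intervention and control group will receive verbal and written information on the baseline measurement". It then gives each arm a different speaker. For the intervention arm: "Employees in the intervention group will be informed verbally by the participatory group (Engine of Development) by presentations at team meetings". For the control arm: "Employees in the control group will be informed by their immediate supervisors during team meetings". The written part is common: "All groups will receive a digital letter with information about the baseline measurement". The section later says that a similar procedure is used at T1 and T2.
- **Phase 1: Needs assessment** introduces the Engine as part of the intervention's first phase ("Therefore, a participatory group of employees is constituted"). The management team picks its members, apart from the facilitator and the researcher, for their perceived capacity to lead change. The group "becomes the project’s ambassador throughout the needs assessment". On timing, the section says: "The intervention kicks off with an information session, held after baseline measurement".
- **Effect evaluation** (under Data analysis) corrects the T1 and T2 effects on primary and secondary outcomes for baseline values.

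**The concern.** A baseline used for correction should be collected in the same way in both arms and before any part of the intervention reaches staff. Here the intervention departments hear about the T0 survey from a group that belongs to the intervention and is meant to promote the project. The control departments have no such group and hear from line management.

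Two things could then differ by arm at T0. One is who responds, because chosen colleagues and supervisors may persuade different people. The other is how respondents answer on vitality, need for recovery, support and efficacy.

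The baseline carries more weight in this trial than in a randomised one. The schools chose the intervention departments, so comparability rests on matched control departments, baseline correction and possibly propensity scores. None of these can separate a real difference at T0 from one produced by the way T0 was announced.

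**Working it through.** The document gives no figure to reproduce. The check compares its sections and then considers what a T0 difference would do to the analysis.

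**Order of events**

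1. The verbal briefing takes place before T0 in both arms (Information provision on measurement).
2. In the intervention arm the Engine gives it. The Engine must therefore already be formed and appearing before staff ahead of T0.
3. The Engine is set up under Phase 1 and acts as ambassador during the needs assessment (Phase 1: Needs assessment).
4. The same Phase 1 section dates the start of the intervention after T0.
5. The explanation of the participatory approach also comes after T0 (Information provision on participatory approach).

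Steps 4 and 5 agree with each other. Steps 2 and 3 put an intervention component in front of staff earlier than step 4 implies. The article does not say when the Engine begins to act.

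**Symmetry between arms before T0**

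| Element | Intervention | Control |
|---|---|---|
| Stated subject | Baseline measurement | Baseline measurement |
| Letter | Digital, all groups | Digital, all groups |
| Who informs management | Facilitator | Facilitator |
| Who informs employees | Engine of Development | Immediate supervisors |

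Only the last row differs.

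**Consequence for a baseline-corrected estimate**

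Let s be the shift in the intervention arm's T0 mean caused by the messenger, c the corresponding artefact at follow-up, and b the baseline-to-follow-up slope, assumed to lie between 0 and 1. The adjusted effect is the follow-up difference minus b times the baseline difference, so

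bias = c − b·s.

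- If the artefact occurs at T0 only, c = 0 and the bias is −b·s. An upward T0 shift understates benefit and a downward shift overstates it.
- If the same messengers produce the same reporting artefact at follow-up, c = s and the bias is (1 − b)·s. It partly cancels, and what remains has the opposite sign to the first case.

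The document gives no value for s, c or b, so neither size nor direction can be computed. The formula also leaves out selective response, which changes who is in the T0 sample; baseline correction need not remove that.

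**The case against.** The strongest reply is that nothing of substance reaches staff before T0. The stated subject is the survey, all groups get a letter, and the approach itself is explained only afterwards. The protocol's own theory has efficacy growing through mastery gained by taking part, and hearing a colleague announce a questionnaire is not taking part. The Engine also meets before, during and after the three needs-assessment steps, so forming it ahead of the staff kick-off is compatible with the Phase 1 description. Expectation will differ by arm anyway, since the schools chose the departments and there is no blinding. Finally, similar messengers at T1 and T2 would partly cancel a constant reporting effect.

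Most of this stands, and it limits the point. It does not remove the different messenger, for which the article gives no reason. The sentence on a similar procedure at follow-up comes directly after the consent paragraph, so it may not cover the choice of speaker. Cancellation would not apply to selective response at T0. The article itself reports strong scepticism among school staff towards surveys, which suggests that the way staff are approached matters for response.

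A reader might also infer that the facilitator contaminates the control arm, because management in the "control group will be informed by the facilitator during a management meeting". The full sentence covers management in both arms, so this creates no difference between arms at T0 and is not part of the point.

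**Conclusion.** The point holds as a difference in procedure between arms, together with an unclear date for when the Engine starts to act. Before T0, a component of the intervention addresses staff in one arm, and the other arm has no counterpart. The resulting T0 values are then used to correct every effect estimate in a non-randomised comparison.

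A reader might go further and infer that the intervention has been delivered before baseline, or that the effect estimate is biased by some stated share of the target. The documents support neither. The content before T0 is limited to the baseline measurement, and any percentage would rest on an assumed shift and an assumed slope. The effect may be small. That it matters at all assumes that the speaker influences who responds at T0 or how they answer.

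It is still worth correcting, because the change is cheap and a baseline that has already been collected cannot be repaired.

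**What to change.** 1. Before T0, use the same type of messenger in all four departments (one intervention and one control department in each of two schools), with one common script alongside the digital letter. The immediate supervisors already used in the control departments are one option. The researcher would not be a clearly neutral choice, being listed as a member of the Engine.
2. Schedule the Engine's first presentation to staff after T0, for example at the information session.
3. Reconcile Phase 1: Needs assessment with Information provision on measurement by stating when the Engine is formed and when it first acts towards staff. State who informs staff at T1 and T2.
4. Report T0 response by department.

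The cost is a short script and some rescheduling. The small downside is losing the ambassadors' help with T0 recruitment in the intervention departments. Supervisors may also affect how candidly staff answer about supervisor support, but the same type of messenger would then be used in both arms. If T0 has already been collected, only items 3 and 4 remain possible, and the different messengers should be reported as a limitation.

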#### Information provision on participatory approach

Then, for both intervention groups a briefing will be held to announce the start of the participatory approach. During the briefing, the participatory approach is explained by the facilitator and the role of all participants is clarified. All questions can be asked. In addition, some of the results of the baseline measurement will be fed back during the meeting. The researchers’ prior experiences in educational institutions have learned that an enormous general skepticism towards survey research has to be overcome before support can be created. Demonstrating that results of the questionnaires are actually used for the better, helps to create support.

#### Information provision during the participatory approach

Continuously informing employees on the progress of each step is inherent to the participatory approach. The proceedings of each step are fed back to all staff of the intervention group, after suggestions from the participatory group and management are taken into account.

## Discussion

In the educational sector, job demands have intensified at rapid pace in recent years, while job resources remained the same. The imbalance between demands and resources contributes to the development of mental health problems such as burnout. At the organizational level burnout resonates in increased sickness absence rates and problems with retention of experienced and novice teachers. Until now, most intervention studies that aimed to target these problems have been only partly effective, possibly because they focused on the individual level and applied secondary preventive interventions. Instead, it has been argued theoretically to focus on the organizational level and application of primary preventive interventions. The current research helps to translate this theoretical reasoning to empirical studies.

This is the first study to describe the test of a participatory, primary preventive organizational level intervention (i.e. a participatory action approach) on work-related stress and well-being that targets and engages all workers in the primary process of vocational education training schools. The goal of this study is to determine whether the participatory action approach, which is supposed to result in tailored, work-oriented solutions on the balance between job demands and job resources, effectively influences need for recovery and vitality.

### Strengths and limitations of the intervention

Less than a quarter of the intervention studies focus on primary preventive interventions, as assessed in a recent meta-analysis on stress interventions [35]. Thus, a first strength of the current intervention is the aim to alter job stress at its core (primary prevention).

Second, by making use of the participatory action approach, stakeholders at all levels are involved - teachers in the first place. This ‘bottom-up’ involvement of all stakeholders likely contributes to commitment to the proposed solutions. Solutions that can count on both the management and the work floor’s commitment are more sustainable and thus more likely to have impact [37,40].

A third strength is that the intervention is conducted in the same way for both schools, but the tailored workplace solutions can differ. This way we can compare different solutions on similar outcomes, further contributing to evidence-based practice.

Fourth, the project requires close collaboration between the intervention provider (i.e. the facilitator) and the researcher. They have a different task to fulfill within the project: the facilitator needs to make the intervention work, the researcher needs to make the study design work. Inevitably, their world views (or: paradigms) will meet and, maybe clash. An issue is that the intervention provider works from a ‘practice-based evidence’ perspective, asking himself at every step: is it useful? Is it important? Is it valid? Whereas researchers aim to contribute to evidence-based practice and therefore ask themselves: is it valid? Is it important? Is it useful? [84]. Even though the differing paradigms and activities will probably make the project difficult from time to time, the primary interest of both intervention provider and researcher is eventually the same: working happier and healthier in vocational education.

#### Strengths and limitations of the study

In line with earlier recommendations (e.g. [86]) the current study assesses all steps of the intervention process, that is: 1) the intended intervention, 2) intended changes in exposure or behavior (i.e. job demands and job resources), and 3) intended changes in study outcomes (i.e. need for recovery and vitality). From an (occupational) epidemiological point of view, the study can be classified as a *prevention-effectiveness study*[86,87] as opposed to the *etiologic intervention study* (i.e. the most rigorous epidemiologic design, derived from the controlled clinical trial, studying disease and health outcomes [87]). Characteristics of the prevention-effectiveness study design are amongst others: small samples, no randomization or blinding, test of a program theory, quantitative and qualitative measures, case studies [88]. These characteristics ensure the internal validity of the study. Prevention effectiveness trials are at the core of evidence-based public health [87,88]. The results of our study will be fed back to the vocational education council and policy makers in the field, helping them to ‘practice evidence-based’. From a sociological, psychological or anthropological point of view, our study would rather be classified as a *pragmatic trial*, designed to find out ‘how effective a treatment actually is in routine, everyday practice’ [89]. Since we are conducting research in practice, several unforeseen events (e.g. reorganization) can take place, which might endanger the feasibility of the study. But our study is designed to reflect what happens in ‘the real world’ [89], maximizing external validity. This asks of the researchers and intervention providers to adjust to unexpected changes, while respecting the ‘intention-to-treat-principle’ (i.e. once allocated to the intervention or control group, always allocated to intervention or control group). Pragmatic trials allow for subtle variations in the intervention and research protocol, so to match the schools’ context and needs. The researchers will not permit any variations in the protocol of the first phase of the intervention (needs assessment), but broad variations are permitted in the second phase of the intervention. In the current study, points of view from the epidemiological, sociological and psychological disciplines are combined, so to maximize both internal and external validity [90].

A strength of the study is that both psychological outcomes (e.g. job satisfaction) as well as organizational outcomes (e.g. sickness absence) are taken into account, contrary to most intervention studies published [35]. The outcomes are assessed qualitatively (i.e. (group) interviews, observations, logs) and quantitatively (i.e. self-report measures in digital survey) and whenever possible complemented with ‘objective’ organizational data (e.g. sickness absence registration).

Besides strengths, the study also comprises possible limitations. A limitation of this study is the quasi-experimental design. However, the study’s design – a controlled trial with departments allocated to conditions and two follow-up measurements - is as rigorous as possible in a practice-based study in (vocational) education. On the one hand, by giving higher management a vote in the choice for the intervention group, selection bias is possibly introduced. On the other hand, higher management’s commitment to the study is assured and thereby relevance and feasibility of the study. A second limitation is the timeframe of the study. Behavioral and organizational changes do not come easy nor quickly. Therefore, the timing of follow-up measurements (six and eighteen months) might be too soon to establish the organizational changes and detect effects.

To conclude, Kristensen [86] reminds occupational intervention researchers of the ‘simple fact that the purpose of workplaces is to produce goods and services – not to serve as arenas for intervention research’. The “Bottom-up Innovation” project will probably encounter numerous unexpected changes, but the design and research methods are chosen carefully, so to optimize both internal and external validity.

